#### 2.5.2. Wait list control group

Participants in this control group will be on a waiting list for 4 months. Afterward, they will receive the self-help micro-video psychological intervention after the study. A waiting list control group is ethically acceptable given that there is no immediate risk or indication for medical treatment (31). At the same time, all members of the wait-in-list will also be screened for regular monitoring and preparedness for emergency intervention protocols and referrals to clinical services as necessary. During this time, they will have unrestricted access to professional help if necessary. The only difference with the intervention group is whether self-help methods are actively taught.

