On WeChat, the most frequently used app in China, the *MVPTC* applet platform is easily accessible to users. Participants can use the platform conveniently in the privacy of their own homes, with more flexibility, and in a relatively anonymous way. Mandatory hospital or treatment room visitations can be reduced after using this platform, and it brings a lot of convenience for participants even in this pandemic era, no matter where they are. This can save transportation time and streamline the treatment process. In addition, the platform’s online application can reduce the time spent with clinicians while minimizing costs, which can make intervention treatment accessible to more populations.

By using the management system of the applet, all participants can be monitored and tracked by the researchers. While the platform does not have a crisis management function, when participants in both groups face the risk of self-injury, suicide, or exacerbating their symptoms of depression and anxiety, researchers still have the option of halting the study after discussed with the research team. Furthermore, participants in this situation can be recommended by researchers to receive emergency medical treatment. If necessary, the participant’s guardian or family member can be contacted to talk about the possible need for higher-level treatment, such as medication or hospitalization. All of this will be informed consent at the beginning of the study.

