### 2.7. Sample size

The results of the pre-experiment were used as a reference for the estimation of the sample size. The preliminary results of the intervention group before and after the intervention in the pre-experiment are shown in Table 1.

From previous studies (39), we know that there was no significant statistical difference between the result of the waiting list control group’s score before and after. Thus, we used the score before the intervention as the outcome score of the waiting list control group and the score after the intervention as the outcome score of the intervention group to calculate the sample size that was based on the two-sample mean to improve the efficiency of the experimental design (40) in the calculation formula when computing the sample size.

(1)
$$\eta_{A}=\kappa \eta_{B}\text{⁢and⁢}\eta_{B}=(1+\frac{1}{k}\,){\left(\sigma \frac{z_{1-\alpha }+z_{1-\beta }}{\mu_{A}-\mu_{B}-\delta }\right)}^{2}$$

κ represents the ratio of two groups of sample size. In this study, κ = *1*. σ stands for standard deviation. In this study, the standard deviation before intervention was considered the population standard deviation. *Z1*-α represents the value of the standard normal distribution function corresponding to the level of class I error (test level). *Z1*-β represents the value of the standard normal distribution function corresponding to the level of class II error (test level); Delta represents the boundary between the two sets of values.

The test level α = 0.05 and the degree of certainty β = 0.20 were set. The combined standard deviation of SDS and SAS as well as the boundary values of different outcome indices (the difference between indices considered to be meaningful professionally) were used to calculate the sample size, as the results are shown in Table 2. In light of feasibility, funding, and other practical factors, the study selected 100 cases in each group, or 200 cases in total, as the sample size.

**TABLE 2 T2:** Minimum sample size of each group required to find differences between groups at different threshold levels.

Outcome indicators	Outcome score of intervention group	Outcome score of control group	Combined standard deviation σ	Boundary value δ	Sample size	Loss rate 30%
SDS	50	61	8	5	22	33
				6	32	43
				7	50	61
				8	88	98
				9	198	209
SAS	42	51	7	4	25	36
				5	38	49
				6	68	79
				7	152	163

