### 2.8. Discontinuation

If the below conditions are met, participants will be able to choose to withdraw or will be required to quit the study:

a.Somatic disease progression.b.Serious adverse events.c.Uncontrollable concurrent disease.d.Whenever the participant wishes to withdraw.e.Poor compliance.f.Instances in which withdrawal from the study can bring more benefits to the participants, including adverse health factors or an increased risk of suicide.

Participants should be clearly informed of their right to withdraw from the study at any time, regardless of their stage of evaluation, treatment, or follow-up. The principal investigator is responsible for the decision to withdraw a participant from the study after consulting other members of the team.

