## 3. Outcome measurements and instruments

The study assessment will be completed online by the subjects on a self-help basis. Self-rating scales were used in this study. The analysis of these scales will be conducted by a statistician without knowing how the subjects are allocated.

The efficacy indicators include (1) the primary outcome: the change in the SDS score and the SAS score between groups at different times. In particular, if the reduction rate is ≥50%, an obvious effect will be shown; if the rate is <50 and ≥25%, the effect is only average; and if the rate is <25%, no clinical effect will exist. (2) The secondary efficacy outcome is based on The Connor-Davidson Resilience Scale (CD-RISC) score, which can be increased as symptoms of anxiety and depression improve during the treatment process. In addition, measurements including the Insomnia Severity Index (ISI) and the Perceived Social Support Scale (PSSS) will be provided.

The applicability indicators include the intervention completion rate, the dropping rate, and the Self-Assessment Scale of the Overall Efficacy and Satisfaction of Participants (SASE) score.

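### Participants can be removed from the whole study for suicide risk, serious adverse events or worsening; scores lost this way are imputed too low by EM, and the SDS difference can be biased in either direction

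*Protocol article*

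**What the plan says.** Section 2.8 introduces its list of conditions with the statement that "participants will be able to choose to withdraw or will be required to quit the study". What is left is the study, not only the modules. The conditions include serious adverse events, "Poor compliance" and "Instances in which withdrawal from the study can bring more benefits to the participants, including adverse health factors or an increased risk of suicide". The principal investigator decides, after consulting the team.

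Section 2.5.3.1 adds that "researchers still have the option of halting the study after discussed with the research team". This option applies "when participants in both groups face the risk of self-injury, suicide, or exacerbating their symptoms of depression and anxiety". The wording could mean stopping only the modules; section 2.8 cannot be read that way.

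For the control arm, section 2.5.2 says that "all members of the wait-in-list will also be screened for regular monitoring and preparedness for emergency intervention protocols". It does not say that this monitoring yields an SDS or SAS score.

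Section 3 makes SDS and SAS change the primary outcome and says: "The study assessment will be completed online by the subjects on a self-help basis". The abstract sets the assessments at baseline, post-intervention, 1 month and 3 months. Section 4 analyses all randomized participants and imputes missing data by EM. Section 5 plans a dropout analysis and a survey of reasons for leaving.

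**The concern.** Suicide risk and worsening depression or anxiety are close to what the SDS and SAS measure, so the removal rule acts on the outcome itself. A removed participant stays in the intention-to-treat analysis only through predicted scores.

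EM predicts from recorded scores. It is adequate when those scores explain why later ones are missing, for example when the worse score is recorded before removal. It is not adequate when someone deteriorates between assessments and is removed first. The missing score is then higher than the recorded history suggests (missing not at random) and is imputed too low. The survey in section 5 collects reasons, not scores.

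If this happens unequally in the two arms, the estimated SDS benefit is biased. Poor compliance can push the other way. If it means not doing the modules, only the intervention arm can be removed for it, and those who did not benefit are filled in with scores typical of those who did.

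**Working it through.** **Formula.** Let benefit = wait-list mean minus intervention mean. In each arm let w be the share lost unscored and g the true minus the imputed score. Each arm mean is too low by w × g, so

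bias in benefit = w_I × g_I − w_C × g_C.

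Negative means understated.

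**Inputs from the documents.**
- Table 1 (SDS): before 61.41, SD 4.92; after 49.63, SD 10.11; difference 61.41 − 49.63 = 11.78.
- Table 2: means 61 and 50, difference 11, SD 8. The pooled SD from Table 1, √((4.92² + 10.11²)/2) = 7.95, reproduces the 8.
- Section 2.3: SDS entry limit 72.

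**Assumptions.** The documents give no removal threshold, removal rate or wait-list follow-up SD. For illustration, everyone whose SDS would exceed 72 leaves before being scored, the correlation with baseline is 0.5, and EM is run within arm. For the wait-list SD, section 2.7 says "the standard deviation before intervention was considered the population standard deviation" (4.92 in Table 1), while Table 2 uses 8; SD 6.5 and SD 10 are added to show sensitivity.

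**Shares lost post-intervention (normal tail above 72).**
- SD 8: wait list (72 − 61)/8 = 1.375, 8.5%; intervention (72 − 50)/8 = 2.75, 0.3%.
- SD 10: 1.10, 13.6%; 2.20, 1.4%.
- Pilot SDs: (72 − 61.41)/4.92 = 2.15, 1.57%; (72 − 49.63)/10.11 = 2.21, 1.35%.
- Wait-list SD 6.5, intervention as in the pilot: 1.63, 5.2%; 1.35%.

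**Gap and bias (single follow-up, simulated, large arms).**

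| Case | Wait list: true / imputed, w × g | Intervention: true / imputed, w × g | Bias |
|---|---|---|---|
| SD 8 | 75.7 / 62.8, 1.09 | 74.4 / 55.9, 0.06 | −1.03 |
| SD 10 | 77.1 / 61.8, 2.06 | 75.5 / 55.7, 0.28 | −1.8 |
| Pilot SDs | 73.7 / 64.1, 0.15 | 75.5 / 55.5, 0.27 | +0.12 |
| Wait-list SD 6.5 | 74.7 / 63.7, 0.57 | 75.5 / 55.5, 0.27 | −0.30 |

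In the pilot case the wait list loses slightly more people, yet the bias is positive because the imputation gap in the intervention arm is about twice as large (20.0 against 9.6 points). The sign changes somewhere between wait-list SD 4.92 and 6.5.

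**Four assessments** (correlation 0.6 between follow-ups, exit at the first score above 72):
- Bias at 3 months is −1.2, −2.1 and +0.15 for SD 8, SD 10 and pilot SDs.
- If only half of those above 72 leave, it is −0.6, −1.05 and +0.08.
- If the worse score is recorded first, it is within 0.02. With the same outcome distribution in both arms, it is within 0.03.
- For SAS, with exit above 69, it is about −0.1 or less in size.

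**A different model** (10-point lasting worsening, 100 per arm, SD 8, correlation 0.5, EM by arm), 3-month bias in benefit:
- Unscored removal of 5% intervention and 15% wait list: −1.0. Reversed: +1.0. At 10% each: about 0.
- With the first worse score recorded, ∓0.4 remains in the two unequal cases.

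**Poor compliance.** Suppose intervention leavers truly score 61 and are imputed near 50. Then 5% lost gives 0.05 × 11 ≈ +0.6 and 10% gives 0.10 × 11 = +1.1. With half the benefit retained, the figures are about +0.3 and +0.55.

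**Significance.** The smallest within-arm estimate above is 11 − 2.09 = 8.91. With SD 10 and 100 per arm the standard error is 10 × √(2/100) = 1.414, so z ≈ 6.3.

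**The case against.** The strongest reply is that this argues from a condensed article. Nothing says that assessments stop when a participant leaves, and the section 5 survey implies contact afterwards. Medication and outside help are allowed (sections 2.5.1 and 2.5.2), so worsening can be managed within the trial, and section 2.5.3.1 gives only an option. This limits how often removal will occur. It does not remove the stated rule that people may be required to quit the study, and a survey of reasons does not supply scores.

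A second reply is that the illustration is artificial. The 72 is an entry limit, not a removal rule, and worsening seen in the applet would often already be scored. Removing 8.5% or 13.6% of a mild-to-moderate wait list by the first follow-up is a lot, and SD 10 for that arm has no source in the documents. With pilot values the bias is only 0.12. All of this stands: the figures show a mechanism and a range, not a forecast.

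Third, section 4 does not say that EM is run within arm. With pooled arms the pilot case falls to about 0 (−0.01), and the SD 8 and SD 10 cases grow to between −1.5 and −1.6 and between −2.5 and −2.7, depending on whether Table 2 or Table 1 means are used. The positive sign in the pilot case therefore depends on within-arm EM. Bias in either direction does not rest on that case alone: more unscored removals in the intervention arm, or removal for poor compliance, also inflate the benefit.

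Finally, recording the worse score first is not a guarantee. It gave about 0 in one model and left 0.4 points in the other. That supports collecting the later scores too.

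**Conclusion.** The concern holds in its conditional form. The protocol's removal rule and its EM imputation combine so that a participant removed before a worse score is recorded is analysed with a score that is too low. The documents settle neither the direction nor the size of the resulting bias. Under the stated assumptions the SDS benefit moves from about −2 points to slightly above 0 for symptom-driven removal with EM within arm, and by +0.6 to +1.1 if 5% to 10% of the intervention arm leave unscored for poor compliance without benefit. It is close to zero if outcome-related loss is equal in both arms and EM is run by arm. SAS is hardly affected in the illustration.

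No conclusion about significance changes at the planned effect. What is at stake is the accuracy of the reported SDS benefit, and scores that were never collected cannot be recovered by a later analysis plan. This is an inexpensive improvement rather than a serious flaw.

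**What to change.** In sections 2.8 and 2.5.3.1, separate two decisions: stopping the modules or referring the participant, and stopping data collection. Unless the participant withdraws consent to follow-up, request SDS and SAS at the time of removal and at the scheduled post-intervention, 1-month and 3-month online assessments, in both arms and whatever the reason, including poor compliance. Within the dropout analysis of section 5, report withdrawals by reason and arm. The clinical rule for choosing between help inside the study and removal remains with the investigators, and the right to withdraw is unchanged.

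The cost is about two sentences of protocol text and a few extra online reminders, since the assessments need no visit. Some referred participants will not respond, so the loss is reduced rather than eliminated. The estimates will include the effect of care received elsewhere, which intention-to-treat already implies.

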## 3. Outcome measurements and instruments

The study assessment will be completed online by the subjects on a self-help basis. Self-rating scales were used in this study. The analysis of these scales will be conducted by a statistician without knowing how the subjects are allocated.

The efficacy indicators include (1) the primary outcome: the change in the SDS score and the SAS score between groups at different times. In particular, if the reduction rate is ≥50%, an obvious effect will be shown; if the rate is <50 and ≥25%, the effect is only average; and if the rate is <25%, no clinical effect will exist. (2) The secondary efficacy outcome is based on The Connor-Davidson Resilience Scale (CD-RISC) score, which can be increased as symptoms of anxiety and depression improve during the treatment process. In addition, measurements including the Insomnia Severity Index (ISI) and the Perceived Social Support Scale (PSSS) will be provided.

The applicability indicators include the intervention completion rate, the dropping rate, and the Self-Assessment Scale of the Overall Efficacy and Satisfaction of Participants (SASE) score.

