**Methods:**

In this parallel-group, randomized controlled trial, a total of 200 mild to moderately depressed and/or anxious adults seeking self-help will be randomly recruited and assigned to either the micro-video psychological intervention group or the wait list control group. Online measurements by self-assessment will be taken at baseline, post-intervention, 1-month, and 3-month follow-up.

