### 1.2. Objectives

In this study, a prospective, parallel-group, randomized controlled clinical trial will be conducted to probe the applicability and efficacy of *MVPTC* on alleviating symptoms and improving mental resilience in participants with mild to moderate depression and/or anxiety.

Specifically, this trial will be designed to see if the symptoms of depression and/or anxiety are significantly reduced and mental resilience is significantly improved in the micro-video psychological intervention group when compared with the wait list control group.

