## 4. Statistical analysis

The analyses will be conducted based on the principle of intention-to-treat, meaning that all participants who have been randomized will be included in the analyses. In statistical tests, the SPSS version 23.0 software will be selected and used. The relevant data will be considered statistically significant if P < 0.05. The categorical variables are statistically described by the number of cases (percentage), and the chi-square analysis is used for intergroup comparison. Continuous variables are statistically described using mean ± standard deviation (M ± SD), and the independent sample *t*-test is used to make comparisons between the two groups. Also, repeated measures, such as ANOVA, are used to compare the degree of symptom improvement between the intervention group and the control group, and the interaction of group × time is analyzed. Missing data will be imputed using the estimation maximization (EM) method in SPSS version 23.0.

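### The primary outcome is two scales over three follow-up times at a flat 0.05, with no deciding time, test or success rule; an either-scale win carries about 8-10% to 15-26% error

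*Protocol article*

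**What the plan says.** The efficacy indicators in section 3 of the protocol article begin with "the primary outcome: the change in the SDS score and the SAS score between groups at different times". On timing, the abstract states: "Online measurements by self-assessment will be taken at baseline, post-intervention, 1-month, and 3-month follow-up". Section 2.6 gives the same schedule, with the post-intervention assessment at the end of the 24-day programme.

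Section 4 sets the threshold once for everything: "The relevant data will be considered statistically significant if P < 0.05". It names two kinds of between-group analysis for continuous scores. For the independent-sample t statistic, the "test is used to make comparisons between the two groups". It also says "repeated measures, such as ANOVA, are used to compare the degree of symptom improvement between the intervention group and the control group", and adds that "the interaction of group × time is analyzed".

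On what counts as success, section 1.2 says only that the trial is designed to "see if the symptoms of depression and/or anxiety are significantly reduced", with resilience alongside. Section 2.7 sets the error rates for the sample size: "The test level α = 0.05 and the degree of certainty β = 0.20 were set". Table 2 then sizes SDS and SAS separately.

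**The concern.** A primary outcome should leave one answer to the question of whether the trial succeeded. Here three things are open: which of the three post-baseline times decides, whether the t-test or the interaction test carries the claim, and whether one scale is enough or both are needed.

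An either-scale win is a realistic reading. Section 2.3 admits people with raised SDS, raised SAS, or both, and section 1.2 uses an and/or wording. Under that reading, the 0.05 in section 4 is the error rate of each test and not of the efficacy claim. Because the choices are open, they could also be made after the results are seen, in favour of whichever scale and time look best.

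This goes beyond a detail that an analysis plan would normally supply. An adjustment procedure may well sit in a plan that is not shown, and its absence here is not the point. The article does define the primary outcome, and its definition makes every follow-up time primary on both scales.

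**Working it through.** **The plan's own figure.** The article states no family-wise error rate; its only error figure is 0.05. Section 2.7 shows how that 0.05 is used. With equal groups its formula is n = 2 × [σ(z₁₋α + z₁₋β)/(difference − δ)]². For SDS with σ = 8, difference 61 − 50 = 11 and δ = 8, using z = 1.645 and 0.842:

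n = 2 × (8/3)² × (2.487)² ≈ 88, as in Table 2.

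All nine sizes in Table 2 reproduce in this way, with a one-sided 0.05. So each scale is sized at the full 0.05, with no sharing between the two.

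**Inputs for the error rate.**
- Scales: 2 (section 3).
- Post-baseline times: 3 (abstract, section 2.6).
- Level per test: 0.05 (section 4). Sidedness is not stated there; two-sided is assumed.
- Correlations between scales and between times: not given. Assumed 0.3 to 0.8, with 0 as the upper bound for the error.
- Success rule: not given. A win on any test is assumed, except where noted.

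**Reading A: one group by time test per scale (2 tests).** If independent, 1 − 0.95² = 9.75%. With correlated tests (simulated, 400,000 draws per setting), using a 3-degree-of-freedom test for two groups at four times:

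| Correlation between scales | Win on either scale |
|---|---|
| 0.3 | 9.6% |
| 0.5 | 9.3% |
| 0.7 | 8.5% |
| 0.8 | 7.9% |

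Two scales compared at a single time give nearly the same: 9.5% at 0.3 and 7.8% at 0.8.

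**Reading B: separate tests at each time (2 × 3 = 6 tests).** If independent, 1 − 0.95⁶ = 26.5%. With correlated tests (same simulation size, between-scale and between-time correlations set equal):

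| Both correlations | Any of six, two-sided | Any of six, favouring the intervention |
|---|---|---|
| 0 (exact) | 26.5% | 1 − 0.975⁶ = 14.1% |
| 0.3 | 24.9% | 12.7% |
| 0.5 | 21.9% | 11.0% |
| 0.7 | 17.7% | 8.9% |
| 0.8 | 15.0% | 7.5% |

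The last column is to be set against a nominal 2.5%.

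**Both scales required, one test each.** The simulated rate is 0.5% at a between-scale correlation of 0.3 and 2.2% at 0.8. It cannot exceed 5%, because each scale must pass its own 0.05 test.

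**Cost of control.** Take 70 evaluable per arm (100 less the 30% loss in Table 2), 80% power, and the Table 2 standard deviations of 8 and 7. The detectable difference is σ × (z + 0.842) × √(2/70), where √(2/70) = 0.169.
- SDS, two-sided 0.05: 8 × 2.802 × 0.169 = 3.8. At 0.025: 8 × 3.083 × 0.169 = 4.2.
- SAS, two-sided 0.05: 7 × 2.802 × 0.169 = 3.3. At 0.025: 7 × 3.083 × 0.169 = 3.6.

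The differences assumed in Table 2 are 11 and 9 points.

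**The case against.** The strongest reply is that section 4 already points to one test per scale. It assigns the comparison of symptom improvement to the repeated-measures analysis, which matches the outcome's wording about change over time and pools the times. The t-test stands in a general sentence, parallel to the one on chi-square tests, and nothing says it is run at each visit for the primary claim. This stands: Reading A is at least as natural as Reading B, and so the lower range has to be given with the higher one.

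A reader might infer that the plan as written lets any one of six tests be claimed as success, so that the error simply is about 17-25%. The documents do not support that. They state no any-win rule; section 3 joins the two scales with and, and the and/or in section 1.2 may only echo the eligible population. The 17-25% figure also needs six time-specific tests and correlations of about 0.3 to 0.7, which the article does not give. And it counts false positives in either direction, including those favouring the wait list.

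Two further points have weight. A full analysis plan may settle the multiplicity procedure, so the lack of an adjustment is not itself a fault. The small cost of control also holds only for a test of no difference. Against the Table 2 boundary of 8 on SDS, where 3 points remain, two-sided 0.025 would need 2 × (8/3)² × 3.083² ≈ 136 per arm. Section 4 names no test against a boundary, so this is a caution and not a refutation.

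What the reply does not remove is that even Reading A has two primary tests and no rule for combining them.

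**Conclusion.** The point holds as a badly fixed primary outcome: two scales, three times, two candidate analyses, a flat 0.05, and no rule that decides success. If either scale can win, the two-sided error is about 8-10% with one interaction test per scale and about 15-26% with separate tests at each time. Counting only results that favour the intervention, the six-test rate is about 7-14% against 2.5%. These ranges rest on assumed correlations of 0.3 to 0.8, with independence at the upper end, and on a two-sided reading of the threshold. If both scales had to succeed on one test each, there would be no inflation above 5%, but the article does not say so. No single figure can be called the trial's error rate, because the choice between these readings is left open.

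**What to change.** Before unblinding, amend sections 3 and 4 as follows.

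1. Name one primary contrast per scale. Either the between-group difference at the post-intervention assessment, which is the comparison the pilot-based sample size uses, or the single group by time test would do. Which one is a design choice for the sponsor.
2. Test SDS and SAS with the Holm procedure at two-sided 0.05: the smaller p-value against 0.025 and, if that succeeds, the larger against 0.05.
3. Report the remaining time points as secondary, with confidence intervals.

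The cost is a few sentences and a small loss of sensitivity. For the post-intervention contrast it is at most the step from 3.8 to 4.2 SDS points and from 3.3 to 3.6 SAS points worked out above. Those figures are for a two-group test of no difference at one time. They do not cover the interaction test or a test against the Table 2 boundary, and would need redoing if either is chosen.
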